### Measures

In general, we aim to examine the effectiveness of our modified secondary distribution models. Primary outcomes of this trial are the number of alters, first-time testing alters, and HIV-positive alters in each arm, therefore, all testers’ information will be specifically clarified and recorded. All data will be collected through JINSHUJU, a secure online platform where participants can apply for HIVST kits, report testing results, and complete the baseline and follow-up questionnaires. All data collected from participants will be examined and deduplicated according to phone number and IP.

In the baseline survey, we will collect the socio-demographic characteristics, sexual orientation, sexual behavior, HIV testing history, and social network. When alters return the results, they will also complete a questionnaire online. In this survey, except for basic information on socio-demographic characteristics, sexual orientation, sexual behavior, HIV testing history, and social network will be collected. We will also investigate the attitudes and experiences towards self-test. The follow-up survey for indexes will take place 3 months after the application completed, which focuses on experiences and attitudes on using and distributing self-test kits. The survey mainly inquires about the occurrence of intimate partner violence (IPV) or other adverse events, the relationship between the indexes and the alters, whether indexes have tested together with the alters, and whether indexes have guided the alters on how to perform HIVST.

Specifically, in our surveys, socio-demographic characteristics include indexes’ age, sex, marital status, the highest level of education completed, and monthly income level. Sexual behavior within 3 months includes previous sex with males and females, role during sex with males, condom use, number of sex partners, and drug use. HIV testing history includes health care facility-based and online HIV testing experience. Social network collects community engagements [7], community connectedness [20], identity fusion [21], and social cohesion [22].

All blood samples will be analyzed using *SD Bioline* HIV/Syphilis duo test kits (*SD Bioline Company*, South Korea). Participants will collect fingertip blood samples by themselves according to the instruction. The trained staff of the CDC or CBO will check and read the photos of result and record them in JINSHUJU. The results are subject to the reading of the staff.

### Missing data plan

Participants will be involved at one to three stages: the baseline questionnaire, results return, and follow-up survey. However, there might be data missing in the primary and secondary outcomes. If there is < 20% of participants missing in the follow-up, a complete-case approach will be applied. If there is ≥ 20% of participants missing in the follow-up, we will investigate the missingness mechanism and use suitable imputation.

### Sample size

According to preliminary study results, on average, the number of alters motivated by an index man was 0.65 through standard secondary distribution, 1.0 through SD/monetary incentives intervention, and 1.4 through SD/monetary incentives plus peer referral intervention. We assumed that the variances of the three groups were equal with the same standard deviation of 0.5 (preliminary data, unpublished results). Further, we estimated an effective sample size of 300 participants (100 in each group), with a power of 0.90, an alpha of 0.05, and a lost to follow-up rate of 0.20.

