### Interventions

#### Standard secondary distribution arm/ control arm

Index MSM in this arm will be eligible to apply for up to 5 HIVST kits based on personal needs, and a 100 RMB (≈ 15 USD) deposit will be charged for each kit. The charged deposit will be refunded to the index if anyone (an index himself or alters to whom he distributed) return his/her testing result. In addition, the participants will need to provide contact information for kits shipping. All kits shipped to a participant will be packed with instructions in an unmarked box to protect privacy. Each kit will be assigned with an identical confirmation code for future distribution tracking, and a unique “ST” number for returned results tracking. After receiving kits, an index can choose to use the kits for themselves or distribute additional kits to alters such as sexual partners or friends. Self-testing kit users can photograph and upload their results to the online platform anonymously by scanning the QR code attached on each kit box. Figure 2 shows the HIVST reporting QR code for testers to return results. Further, alters will be asked to fill out a survey regarding their experience of and attitude toward HIVST. After the survey is completed, the deposit will be returned to the matched index by tracking the confirmation code.

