#### Secondary distribution with monetary incentives plus peer referral (SD/monetary incentives plus peer referral) arm

Index MSM in this arm will first receive the same intervention as the participants received in the monetary incentives arm. In addition, apart from applying for up to five self-testing kits, each index MSM in this arm will obtain a unique referral link, which can be shared with up to 5 individuals within their social network to apply for kits, and each alter can apply for only one kit through the link. Similarly, indexes will be given 20 RMB for each matched alter who returns the result (whether through peer referral or direct distribution). All testers will receive a monetary incentive of 20 RMB once they complete uploading their results.

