### Outcomes

The primary outcomes of this trial consist of three parts: 1) Mean number of motivated alters who have photo-verified self-testing per index in each arm; 2) Proportion of first-time HIV testing among alters in each arm; 3) Proportion of alters with a positive HIV testing result in each arm.

The secondary outcomes of this study consist of three parts 1) Risky sexual behavior among indexes and alters in each arm; 2) Adverse events reported during secondary distribution among indexes and alters in each arm; 3) Attitude towards and past experiences of HIVST and sexual behavior among alters in each arm.

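### The sample-size inputs give about 165 participants, not 300, and the SD of 0.5 is implausibly small for a count of alters, so the single 0.90 does not describe the power for H1, H2 and H3

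*Protocol article*

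**What the plan says.** The first primary outcome in the Outcomes section is the "Mean number of motivated alters who have photo-verified self-testing per index in each arm". The Primary analysis section compares these means with two-sample t-tests for all three pairs of arms, which correspond to H1, H2 and H3.

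The Sample size section reports that "the number of alters motivated by an index man was 0.65 through standard secondary distribution, 1.0 through SD/monetary incentives intervention". The figure for the third arm is "1.4 through SD/monetary incentives plus peer referral intervention". On the spread it says: "We assumed that the variances of the three groups were equal with the same standard deviation of 0.5 (preliminary data, unpublished results". From these inputs it concludes: "we estimated an effective sample size of 300 participants (100 in each group), with a power of 0.90, an alpha of 0.05", with 20% loss to follow-up. It does not say which contrast the 0.90 refers to, or whether the test is one- or two-sided.

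The Interventions section sets the range of the count. A control index "will be eligible to apply for up to 5 HIVST kits based on personal needs"; the incentives arm follows the same application process. The third arm adds a referral link "which can be shared with up to 5 individuals within their social network to apply for kits". An index can therefore generate at most 5 alters in the first two arms and at most 10 in the third.

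**The concern.** Two things look wrong. First, a difference of 0.35 with an SD of 0.5 is a standardised effect of 0.7, which does not call for 100 per arm at 90% power. Second, 0.5 is a very small SD for a whole-number count with means between 0.65 and 1.4 and a ceiling of 5 or 10.

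The stake is the reading of H1 and H3, which rest on differences of only 0.35 and 0.40. One power figure of 0.90, attached to no contrast, invites the reader to treat a null result on either as well powered. Whether it would be depends on the SD.

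**Working it through.** **Inputs.** Means 0.65, 1.0, 1.4; SD 0.5; alpha 0.05; power 0.90; loss 0.20; 100 per arm (Sample size). Two-sample t-tests (Primary analysis). Assumed here because not stated: two-sided and unadjusted for multiplicity.

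**1. Attempt to reproduce 300.** n per arm = 2 (z₀.₉₇₅ + z₀.₉₀)² SD² / Δ².

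- H1, Δ = 0.35: 2 × (1.960 + 1.282)² × 0.25 / 0.1225 ≈ 42.9, so 43; the exact t calculation gives 43.9, so 44. After loss, 43.9 / 0.80 = 54.8, so 55 per arm and 3 × 55 = 165.
- H3, Δ = 0.40: 33.8, or 42.3 after loss, so 43 per arm and 129 in total.
- H2, Δ = 0.75: 11 per arm, 14 after loss, 42 in total.

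Other readings also miss 300:

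| Reading (Δ = 0.35 where a contrast is needed) | Total after loss |
|---|---|
| One-sided 0.05 | 132–135 |
| Bonferroni over 3 tests | 210–216 |
| Bonferroni over 9 tests | 255–264 |
| One-way ANOVA across arms | 46–47 |
| 0.5 read as a variance (86, then 108 per arm) | 324 |

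(Ranges are normal approximation to t, except for ANOVA, where the range is rounding.)

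Power on the stated inputs for Δ = 0.35 is 0.993 with 80 per arm and 0.998 to 0.999 with 100. For the other two contrasts it is about 0.999 or more.

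**2. What SD 0.5 implies for a whole-number count.** The smallest SD a whole-number variable can have is √[f(1 − f)], where f is the fractional part of the mean.

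- Mean 0.65: √(0.65 × 0.35) = 0.477.
- Mean 1.4: √(0.4 × 0.6) = 0.490.
- Mean 1.0: 0, so there is no such floor.

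The following bounds need no distributional assumption.

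- Control: E[X(X − 1)] = 0.25 + 0.65² − 0.65 = 0.0225. X(X − 1) is at least 2 when X ≥ 2, so P(X ≥ 2) ≤ 0.0225 / 2 = 1.1%.
- Incentives: E[(X − 1)²] = 0.25, so at least 75% have exactly one alter.
- Incentives plus referral: E[(X − 1)(X − 2)] = 0.25 + 1.96 − 4.2 + 2 = 0.01. The product is 0 at X = 1 or 2 and at least 2 elsewhere, so at most 0.5% have 0 or more than 2, and at least 99.5% have exactly 1 or 2.

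**3. How large the SD can be.** The largest common SD that keeps 0.90 power is Δ√(n/2) / 3.2415. For H1 this is 0.35 × √40 / 3.2415 = 0.68 at 80 per arm and 0.35 × √50 / 3.2415 = 0.76 at 100 per arm. For H3 it is 0.78 and 0.87.

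**4. Power under count-type variance.** The documents give no other SD, so these variances are assumptions. Power ≈ Φ(Δ / √[(v₁ + v₂)/n] − 1.96), with v = mean for Poisson (SDs 0.81, 1.00, 1.18) and v = mean + mean²/k for the negative binomial (k = 1: SDs 1.04, 1.41, 1.83).

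Example, H1 Poisson at 80 per arm: √(1.65/80) = 0.1436; 0.35/0.1436 − 1.96 = 0.477; Φ = 0.68.

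| Variance, n per arm | H1 | H3 | H2 |
|---|---|---|---|
| Poisson, 80 | 0.68 | 0.64 | >0.99 |
| Poisson, 100 | 0.78 | 0.73 | >0.99 |
| Neg. binomial k = 1, 80 | 0.43 | 0.34 | 0.89 |
| Neg. binomial k = 1, 100 | 0.52 | 0.41 | 0.95 |

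Capping counts at 5, 5 and 10 with the means held fixed leaves the Poisson rows essentially unchanged. It raises the k = 1 figures at 80 per arm to 0.47 (H1), 0.36 (H3) and 0.90 (H2).

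**The case against.** The strongest reply is that the mismatch runs in the safe direction: 300 is about 1.8 times the 165 that the inputs require. Three primary outcomes and three comparisons could justify a larger number, and an article may leave the contrast, sidedness and multiplicity rule to the full protocol. This stands as far as it goes. The 300 is not too small on the stated inputs, and the missing details alone would be no finding. But inputs and result appear together, and no reading tried links them.

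The second reply is that the SD comes from preliminary data which the reader cannot see, whereas the Poisson and negative binomial variances come from outside the document. The deposit of 100 RMB per kit may also hold down large counts. This stands too: the shortfall for H1 and H3 is conditional on the true SD. It does not make 0.5 credible in the referral arm, where practically every index would need one or two verified alters and almost none could have zero or three.

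Three stronger readings are tempting but not supported.

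- A reader might infer that SD 0.5 is impossible. It lies above the minimum in every arm, and in the incentives arm, which enters both H1 and H3, the minimum is 0.
- A reader might infer that the trial is underpowered. The documents neither state nor exclude an SD above 0.68 to 0.76.
- A reader might infer that the 20% inflation is superfluous because the outcome is read from the platform. The Missing data plan expects possible gaps in the primary outcomes, so power should be shown at both 80 and 100 per arm.

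**Conclusion.** The point holds in two parts. The stated inputs give 165 participants, not 300, for the smallest contrast (two-sided, unadjusted); on those inputs the design has power of 0.99 or more, not 0.90. Separately, SD 0.5 is only just above the minimum possible in the control and referral arms and is implausibly small for this outcome.

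The 0.90 is therefore not a reliable description of any of the three hypotheses. Assuming Poisson variance at the planned means, H1 and H3 have about 0.68 and 0.64 at 80 per arm, or 0.78 and 0.73 at 100, and less with overdispersion. H2 keeps about 0.89 or more down to negative binomial k = 1. How far H1 and H3 fall short cannot be settled until the preliminary SDs are reported.

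**What to change.** Keep 300 and rewrite the Sample size paragraph:

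- Report the SD of alters per index in each arm of the preliminary data, and confirm that 0.5 is an SD and not another quantity, such as a variance or a standard error.
- State the contrast and the sidedness behind the calculation.
- Replace the single 0.90 with power for each of H1, H2 and H3 under count-type variance (Poisson and overdispersed), at 80 evaluable and at 100 per arm.
- Say which contrast has 0.90 power. On the assumptions above this is H2, up to roughly k = 1.

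The cost is one rewritten paragraph, with no extra participants and no change to arms or analysis. The Trial status section says that statistical analysis has not begun, so the correction can still precede the results. The downside is that the stated power for H1 and H3 is likely to become less favourable.

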#### Primary analysis

We will first calculate primary outcomes in each arm, i.e., mean number of alters that each index recruited, proportion of first-time HIV testers, and proportion of alter testers with an HIV-positive result. Secondly, we will compare calculated means using two-sample t-test, and proportions using chi-square between SD/monetary incentives arm and control arm, SD/monetary incentives plus peer referral arm and control arm, and also between two intervention arms.

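### The single power of 0.90 rests on alters per index only; for the two primary proportions among alters, the implied denominators give 0.90 power only for large differences

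*Protocol article*

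**What the plan says.** The Outcomes section states that "The primary outcomes of this trial consist of three parts": the mean number of photo-verified alters per index, then "Proportion of first-time HIV testing among alters in each arm", then "Proportion of alters with a positive HIV testing result in each arm". No order or lead outcome is given. The Primary analysis section compares means by two-sample t-test and "proportions using chi-square between SD/monetary incentives arm and control arm", and does the same for the other two arm pairs.

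The Sample size section takes its inputs from preliminary data, with a mean of 1.4 for the arm that adds referral links; for the other two, "the number of alters motivated by an index man was 0.65 through standard secondary distribution, 1.0 through SD/monetary incentives intervention". It assumes that "the variances of the three groups were equal with the same standard deviation of 0.5". From these it arrives at 300 indexes, 100 per arm, "with a power of 0.90, an alpha of 0.05, and a lost to follow-up rate of 0.20".

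The protocol gives no expected rate and no target difference for first-time testing or for HIV positivity among alters. The nearest figure is the 7% HIV prevalence among MSM in Zhuhai, in Study setting and recruitment.

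**The concern.** A mean and an SD of alters per index carry no information about the power to compare two proportions among those alters. The denominator for outcomes 2 and 3 is the number of alters who test, and the plan's own means make that number small, above all in the control arm. Yet only one power figure appears, next to three primary outcomes of equal standing.

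The two proportions are not peripheral. The Background singles out first-time testers among alters, and the Objectives include reaching first-time testers and identifying people with reactive results. Suppose a chi-square test on either outcome is non-significant in a trial described as having 0.90 power. A reader could take it as evidence that the arms reach similar people, and the design supports that reading only if large differences are the ones of interest.

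**Working it through.** **1. Outcome 1: the plan's own figure.** Inputs from Sample size: smallest difference 1.0 − 0.65 = 0.35; SD 0.5; power 0.90; alpha 0.05 (two-sided assumed, as sidedness is not stated); loss 20%.

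n per arm = 2(1.960 + 1.282)² × 0.5² / 0.35² = 2 × 10.51 × 0.25 / 0.1225 = 42.9, so 43 (44 with the t distribution). After 20% loss: 43 / 0.8 = 53.75, so 54 (44 / 0.8 = 55).

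The stated 100 per arm is not reproduced. Taking the sample size as given, power = Φ(0.35 / (0.5 × √(2/n)) − 1.960). This is 0.993 at n = 80 and 0.999 at n = 100. On its own inputs the plan exceeds 0.90 for outcome 1.

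**2. Alters available for outcomes 2 and 3.** Mean alters per index × indexes per arm:

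| | Control | Incentives | Incentives + referral |
|---|---|---|---|
| 100 indexes | 65 | 100 | 140 |
| 80 indexes | 52 | 80 | 112 |

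The second row applies only if losing an index also loses his alters.

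**3. Power of the pairwise chi-square tests.** Two-sided 0.05, alters treated as independent, lower rate placed in the arm with fewer alters:

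power ≈ Φ((|p₂ − p₁| − 1.960·s₀) / s₁), where s₀ = √(p̄(1 − p̄)(1/n₁ + 1/n₂)), p̄ is the pooled rate, and s₁ = √(p₁(1 − p₁)/n₁ + p₂(1 − p₂)/n₂).

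Example: control versus incentives, 65 and 100 alters, 7% versus 14%. p̄ = (65 × 0.07 + 100 × 0.14)/165 = 0.1124; s₀ = 0.0503; s₁ = 0.0470; (0.07 − 1.960 × 0.0503)/0.0470 = −0.61; power 0.27.

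Ranges over the three arm pairs and both rows of denominators:

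| Scenario (assumed) | Power |
|---|---|
| First-time share +10 points, from 20–40% | 0.20–0.41 |
| First-time share +15 points, from 20–40% | 0.39–0.72 |
| First-time share +20 points, from 20–40% | 0.62–0.92 |
| Positivity 7% vs 14% | 0.22–0.39 |
| Positivity 7% vs 21% | 0.59–0.87 |

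Exact enumeration of the uncorrected chi-square test for a selection of these scenarios agrees within about 0.03.

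**4. Difference needed for 0.90 power**, solving the same formula:

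- First-time share, reference 20–40%: about 19 to 28 points (19 to 25 with 65/100/140 alters).
- Positivity against 7%: about 15 to 22 points, that is about 22% to 29% (22% to 26% with 65/100/140 alters).

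**5. Alters needed for smaller differences.** For control versus incentives at 0.90 power, keeping the 65:100 ratio, about 394 control alters are needed for 30% versus 40%, and about 335 for 7% versus 14%. The plan implies 52 to 65.

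**The case against.** - **The paragraph shows what it calculates.** Its inputs are all alters per index, and the three hypotheses also concern only how many kits are distributed. This stands. A reader might infer that the protocol claims 0.90 for all three outcomes, but it does not say so. The fault is narrower: the figure is not tied to an outcome, while three outcomes are called primary without rank.
- **An article may leave power for the other outcomes to a fuller document.** This is fair as to the missing calculations. It does not cover a published power statement that leaves its outcome unnamed beside three unranked primaries.
- **The low power figures depend on assumed differences.** This stands. A reader might infer that power for outcomes 2 and 3 simply is 0.2 to 0.4. The documents fix neither a reference rate nor a target difference, and at 15 or 20 points power is much higher. The 7% is prevalence among local MSM, not positivity among alters.
- **The 20% loss may not apply to alters.** The follow-up survey is the index's, at 3 months, whereas alters supply results and testing history when they upload. The smaller denominators are therefore a lower case. Dropping them leaves power at 0.24 to 0.41 for 10 points and 0.27 to 0.39 for 7% versus 14%, so the conclusion is unchanged.
- **The Measures section describes the primary outcomes as numbers of alters.** Counts of first-time or positive alters would need a different calculation. The figures here apply to the proportions defined in Outcomes and tested in Primary analysis.
- **Nothing says that a non-significant result will be read as equal reach.** True; that is a risk in interpretation, not a stated plan.

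**Conclusion.** The point holds in this form: the stated power comes from outcome 1 inputs and does not carry over to the other two primary outcomes. At the alter numbers implied by the plan's own means, the chi-square tests reach 0.90 power only for large differences, about 19 to 28 points in first-time share or positivity of about 22% to 29% against 7%. This rests on a two-sided 0.05 level without adjustment for multiple tests, an assumed first-time reference rate of 20% to 40%, the 7% local prevalence as a stand-in for alters, and independent alters. Positive correlation among alters of the same index would lower power further.

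A reader might also infer that 0.90 is at least right for outcome 1. The inputs do not give it: they yield about 0.99 with 80 to 100 indexes per arm. Whether an SD of 0.5 suits such a count is a separate question. If the variance equalled the mean (an assumption), power for 0.65 versus 1.0 would be about 0.68 to 0.78.

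**What to change.** In the Sample size section:

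- Say that the sample size and power calculation covers outcome 1 only, and name outcome 1 as the outcome the trial is powered for.
- Restate its power from its own inputs (about 0.99 at SD 0.5 with 80 to 100 indexes per arm) rather than repeating 0.90.
- Give the expected number of alters per arm and the detectable differences for outcomes 2 and 3, with the assumed reference rates, level and independence stated.

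In the Primary analysis section, report outcomes 2 and 3 as estimated differences with confidence intervals, and state that a non-significant result on them will not be read as no difference.

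The cost is wording, and a less favourable power statement for two outcomes. No more participants are needed. The Trial status section says that statistical analysis has not begun, so on that account the change can precede the results.

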### Data analysis

All statistical analyses will follow the intention-to-treat principle. Missing data will be handled by multiple imputations. Categorical variables from the baseline survey will be aggregated in frequency distributions, and numerical variables will be summarized in mean and standard deviation.

#### Primary analysis

We will first calculate primary outcomes in each arm, i.e., mean number of alters that each index recruited, proportion of first-time HIV testers, and proportion of alter testers with an HIV-positive result. Secondly, we will compare calculated means using two-sample t-test, and proportions using chi-square between SD/monetary incentives arm and control arm, SD/monetary incentives plus peer referral arm and control arm, and also between two intervention arms.

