### Trial design

This is a three-arm randomized controlled trial among Chinese MSM. Enrolled indexes will be randomly assigned to one of the three groups: standard secondary distribution, secondary distribution with monetary incentives arm, and secondary distribution with monetary incentives plus peer referral. Further, indexes will be asked to complete a baseline survey at the beginning of the trial, and a three-month follow-up survey after their HIVST kits applications. A flowchart of the trial is shown in Fig. 1.

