### Allocation

Randomization will be completed by a computer-generated program with a 1:1:1 allocation ratio. A consented participant will be allocated to one of three study groups, i.e., standard secondary distribution group, secondary distribution with monetary incentives group, and secondary distribution with monetary incentives plus peer referral group.

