#### Secondary analysis

Results of the follow-up survey for indexes and the survey for alters will be used for measuring secondary outcomes, i.e. risky sexual behavior, adverse events during secondary distribution, and experience and attitude towards HIV testing. High-risk sexual behavior, defined as unprotected sex, substance use, or multiple sexual partners, are determined from survey questions such as “How often do you wear a condom during anal sex?”, “In the past three months, how many sexual partners did you have?”, “In the past three months, have you used drugs before sex?”, etc. Adverse events or IPV that happened on alters during distribution are determined from the question “Have you experienced any of the following IPV when received the HIVST kit from the index?”. Alters’ experience and perception of HIVST are determined from total 20 question items, e.g. “How difficult do you feel about completing HIV self-testing?”, “How many men did you have anal sex with after HIV self-testing?”, “Which testing do you prefer, facility-based testing or HIV self-testing?”, etc. We will use chi-square tests to compare each outcome of interests between SD/monetary incentives group and control group, SD/monetary incentives and peer referral group and control group, and also between two intervention arms.

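### Alter-level proportions are compared with ordinary chi-square although alters are clustered within the randomised index, so p-values are too small by an amount that depends on an unknown ICC and on the spread of alters per index

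*Protocol article*

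**What the plan says.** **Unit of randomisation.** Trial design: "Enrolled indexes will be randomly assigned to one of the three groups". Allocation: "Randomization will be completed by a computer-generated program with a 1:1:1 allocation ratio".

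**Unit of observation.** Under Outcomes, the second and third primary outcomes are "Proportion of first-time HIV testing among alters in each arm" and "Proportion of alters with a positive HIV testing result in each arm". Both have alters in the denominator. Several secondary outcomes are also measured in alters: risk behaviour, adverse events including IPV, and attitudes to self-testing.

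**Alters per index.** In every arm an index may apply for up to 5 kits, use them himself or "distribute additional kits to alters such as sexual partners or friends". In the referral arm he also gets a link "which can be shared with up to 5 individuals within their social network to apply for kits", so one man can contribute up to 10 alters there.

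**Tests.** Primary analysis: "we will compare calculated means using two-sample t-test, and proportions using chi-square between SD/monetary incentives arm and control arm". The same sentence goes on to the other two pairs of arms. Secondary analysis: "We will use chi-square tests to compare each outcome of interests between SD/monetary incentives group and control group", again for all three pairs.

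The article does not mention clustering, an ICC, a design effect, GEE, a mixed model or robust standard errors. The Sample size section works on the mean number of alters per index and states no power for any alter-level proportion.

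**The concern.** Pearson's chi-square treats each alter as an independent observation. In this design neither recruitment nor treatment assignment happens alter by alter: one man is randomised, and the alters who follow are his partners and friends. Testing history and HIV status may well be alike within such a circle. The IPV question asks alters about receiving the kit from the index, so one index can generate several events.

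With positive within-index correlation, the alters carry less information than their number suggests, and chi-square rejects a true null more often than its nominal level. First-time testing among alters is singled out at the end of the background section as part of the trial's main purpose, so a falsely significant difference there would matter for the trial's message.

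The protocol names a specific test whose independence assumption the design breaks. This is therefore not a detail left open for an analysis plan.

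**Working it through.** **Inputs from the article.** 100 indexes per arm. Mean alters per index: 0.65 (control), 1.0 (incentives), 1.4 (incentives plus referral). SD of alters per index: 0.5 in every arm. Expected alters: 65, 100 and 140. HIV prevalence: 7%.

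**Assumed.** ICC 0.1 to 0.3; a first-time testing proportion of 30% or 40% in simulations; count distributions other than SD 0.5.

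**The plan's own figure.** The stated 300 rests on the mean count. Its smallest planned difference (0.35, SD 0.5, two-sided 0.05, power 0.90) needs 43 per arm, or 54 after 20% loss, 162 in total. So 300 is not reproduced but is more than its inputs need. This does not bear on the present point, because no size or power is stated for the alter-level proportions.

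**Step 1, design effect per arm.** DE = 1 + (E[m²]/E[m] − 1) × ICC, where m is alters per index and E[m²] = SD² + mean².

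- SD 0.5: (0.25 + 0.4225)/0.65 = 1.035; (0.25 + 1)/1.0 = 1.25; (0.25 + 1.96)/1.4 = 1.579.
- Poisson: 1 + mean = 1.65, 2.0, 2.4.

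**Step 2, pairwise inflation and true error.** VIF = (DE₁/n₁ + DE₂/n₂)/(1/n₁ + 1/n₂), with n the number of alters. True alpha = 2 × [1 − Φ(1.96/√VIF)].

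Example, referral vs control, SD 0.5, ICC 0.3: DEs are 1.174 and 1.010. VIF = (1.174/140 + 1.010/65)/(1/140 + 1/65) = 1.062, so true alpha = 5.7%.

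| Counts | ICC | Incentives vs control | Referral vs control | Referral vs incentives |
|---|---|---|---|---|
| SD 0.5 | 0.1 | 5.1% | 5.2% | 5.5% |
| SD 0.5 | 0.3 | 5.4% | 5.7% | 6.4% |
| Poisson | 0.1 | 5.9% | 6.0% | 6.4% |
| Poisson | 0.3 | 7.8% | 8.2% | 9.2% |

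At ICC 0.3 the expected 65/100/140 alters are worth about 64/93/119 (SD 0.5) or 54/77/99 (Poisson).

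**Step 3, simulation under the null.** Beta-binomial outcomes, 100 indexes per arm, 40% first-time testers, 0.65 vs 1.4 alters, ICC 0.1 to 0.3: chi-square rejects in 5.4-6.2% (SD 0.5), 6.0-7.7% (Poisson) and 8-13% (negative binomial, k = 0.5, the stress case).

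**Step 4, is SD 0.5 realistic?** The smallest SD for whole-number counts is √(0.65 × 0.35) = 0.477 at mean 0.65 and √(0.4 × 0.6) = 0.490 at mean 1.4. An SD of 0.5 is possible but leaves almost no room:

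- In the referral arm, E[(m−1)(m−2)] = 0.25 + 1.96 − 4.2 + 2 = 0.01. This product is at least 2 for any index with zero or with three or more alters, so at most 0.5% of indexes can have such counts.
- In control, E[m(m−1)] = 0.25 + 0.4225 − 0.65 = 0.0225, so at most about 1.1% can bring in two or more.

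With 5 kits on offer, and 5 referrals besides in one arm, a wider spread is likely.

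**Step 5, HIV positivity.** At 7%, control expects 65 × 0.07 ≈ 4.6 positives. Simulated chi-square error is about 5.2-5.4% with SD 0.5. With Poisson counts it is about 5% at ICC 0.05, rising to 7.5-9.0% across the three comparisons at ICC 0.3.

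**Step 6, after the change.** At a proportion of 30% and ICC 0.1 to 0.5, a test with index-clustered robust variance rejects in 5.0-5.5% (SD 0.5) and 5.4-5.9% (Poisson). Ordinary chi-square rejects in 5.2-7.5% and 5.9-11.9%.

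**The case against.** The strongest reply is about size. Every large figure needs inputs that the documents do not supply. With the protocol's own means and SD, the excess over 5% is at most about half a point at ICC 0.1 and about 1.4 points at ICC 0.3. The article attributes the SD to preliminary data that cannot be inspected, and 0.5 is tight but not impossible. All three hypotheses and the sample size concern kits or alters per index, and the t-test on that count works at the randomised unit. This all stands, and it limits the weight of the point. It does not remove the point, because chi-square is fixed for two stated primary outcomes and Step 4 shows how little spread the small figures allow.

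A reader might infer more than the documents support:

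- **That the error exceeds 5% for every alter outcome.** This depends on a positive ICC that nobody has reported. For HIV positivity with narrow counts the error stays close to 5%.
- **That clustering is always heavier in the arms with more alters.** With an equal SD of 1.5, E[m²]/E[m] is 4.11, 3.25 and 3.01 for control, incentives and referral, so the order reverses.
- **That confidence intervals will be too narrow.** The analysis sections plan tests only and announce no intervals.
- **That the kit confirmation code links every alter to his index.** That code is on kits shipped to the index. Alters who apply for themselves are tied to him by the referral link.
- **That any cluster-robust test cures the problem.** At 7% positivity, uncorrected robust tests were off nominal: 2.5-4.4% for a logistic Wald test and 5.5-7.3% for a risk difference.

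**Conclusion.** The point holds. The planned chi-square ignores that alters are nested in the randomised index, and with any positive within-index correlation its p-values are anti-conservative for the second and third primary outcomes and the alter-level secondary outcomes.

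The direction follows from the design. The size rests on an assumed ICC and on how widely alter counts vary. For first-time testing at ICC 0.1 to 0.3, the true error is about 5-6% with the stated SD, about 6-9% with Poisson counts, and about 8-13% only under strong overdispersion. I regard the Poisson range as more realistic than the stated SD. For HIV positivity the inflation is near nil unless counts are wider and the ICC higher.

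Outcomes with one value per index, including the t-test on alters per index, are unaffected, so nothing here undermines the comparison on which the trial was sized.

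**What to change.** 1. For every alter-level comparison, replace chi-square with an analysis clustered on the index: GEE with independence working correlation and robust standard errors with a small-sample correction, or a Rao-Scott chi-square.
2. For rare outcomes such as HIV positivity and IPV, use a permutation test that reassigns whole indexes. Base it on a studentised statistic (the difference divided by its cluster-robust standard error). The arms are expected to differ in alters per index, so indexes are not exchangeable even when the proportions are equal. For an unstudentised difference, referral vs control with no ICC, the permutation variance is proportional to 2/102.5 = 0.0195, while the true one is proportional to 1/65 + 1/140 = 0.0225. The ratio of 1.15 alone gives an error of about 6.8%.
3. State that alters are linked to their index by the kit confirmation code or, in the referral arm, by the unique referral link. The platform already needs this matching to pay deposits and incentives.
4. Leave the index-level analyses as they are in this respect.

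The cost is slightly larger p-values, a few sentences of analysis text and a little more programming, with no new data. The Trial status section says that statistical analysis had not begun at the time of writing, so the change should be fixed in writing before any comparison by arm is seen.
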